## Abstract

There is a plausible association between shift work and cardiovascular disease (CVD), which may be due to disruption of the circadian rhythm causing hormonal changes and metabolic disturbances, resulting in high blood pressure, atherosclerosis, diabetes, and being overweight. However, few studies have investigated the association between several consecutive long work shifts, including night shifts, and risk factors for developing CVD. Moreover, knowledge is lacking on factors that may modify or enhance this suggested relationship. The study period is planned from the third quarter of 2018 to the fourth quarter of 2021, and will involve 125 industrial employees at two Norwegian enterprises producing insulation. The work schedule is either rotating shiftwork (morning, evening, night) or regular day work. At baseline, we will measure blood parameters, including markers of inflammation, lipids, and glycosylated hemoglobin. We will also collect measures of blood pressure, resting heart rate, arterial stiffness, carotid intima-media thickness, and aerobic fitness. At the end of baseline data collection, a subgroup will undergo a supervised high-intensity interval training intervention for eight weeks, initiated by the Occupational Health Service. At one-year follow-up, we repeat baseline measures with added measures of heart rate variability and additional five weeks monitoring of sleep and physical activity, and assessment of respirable dust. At the two year follow-up, we will measure CVD risk factors before and after a planned three-month shutdown in one of the studied plants. We will also assess respirable dust, monitor sleep, and compile a one-year retrospective detailed overview of working hours. A final data collection, similar to the one at baseline, will be carried out after three years. We will use a comprehensive set of methods to identify the effects of shift work with long working hours and night shifts on cardiovascular health. This will provide new knowledge on the association between early manifestations of CVD and occupational exposure to shift work. Further, we can study whether work organization such as extensive overtime, sleep loss, and dust exposure have detrimental effects, and if a three-month cease in shift work or increased physical activity will modify early manifestations of CVD.

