### 2.1. Setting and Study Population

We will include two Norwegian enterprises (Plant A and Plant B) which are mainly involved in the production of insulation products. All employees (*n* = 213) will be informed of the research project via information meetings carried out by the Occupational Health Service in collaboration with plant representatives, and will be given the opportunity to participate. Based on previous experience, we expect that approximately 60% of the workers will accept the invitation. Baseline and follow-up measurements will be carried out over a period of three years in order to collect relevant data from the study participants. Overall, data collection consists of a questionnaire, a work hours register, aerobic capacity testing, and medical examinations with measurements of blood pressure, arterial stiffness, cIMT, and blood sampling. Additionally, we will include measures on sleep, physical activity, and respirable dust. The study has been approved by the Regional Ethics Committee in Oslo, REC South East B (Reference number: 2018/1258).

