### 2.2. Exclusion Criteria for Participation

Subjects will be excluded from participation if diagnosed with severe heart or lung disease, cancer, or if they are showing very high blood pressure levels at the medical examination (>180/110). In subjects where unknown medical issues are discovered during examinations, the affected individual will be assigned to an appropriate medical institution or their general practitioner for further investigation.

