### 2.4. Data Collection Procedure at Baseline

#### 2.4.1. Questionnaire

At baseline, subjects will answer a self-administered questionnaire regarding education level, work experience, medication use and history, and lifestyle factors. This will include specific questions on diseases and illness, medicines, with additional focus on those affecting the cardiovascular system, e.g., blood pressure and cholesterol lowering medication, type and quantity of physical activity, smoking habits, type of shiftwork, work history, and previous shift work.

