### 2.5. Physical Activity Intervention

The PA intervention will be carried out by the local Occupational Health Service, with support from Kristiania University College, School of Health Science. The intervention group will consist of all volunteering shift workers in plant A (out of 51 eligible workers), while a control group of shift workers will be recruited from plant B (out of 55 eligible workers). Subjects in the intervention group will perform three supervised training sessions per week for eight weeks. Training sessions will be carried out on a work site in the enterprise’s own training facilities, and will be guided by a physical therapist. Based on participant’s own choice, sessions will be performed by cycle ergometer, row machine, steep hill walking, or running. Dedicated motivators will log all performed sessions during the eight-week intervention period, and will afterwards continue to motivate coworkers to undertake regular PA during the three-year follow-up. The motivators will have regular meetings with the project leaders throughout the follow-up period. The total duration of an interval session will be 17 min, including 10 min warm-up and 3 min cool-down at 60–70% maximal heart rate (HRmax) [29]. During warm-up, participants should not experience any shortness of breath, and ideally, should rate their perceived exertion to be 11–13 on a Borg scale [30]. In extension of the warm-up, the subject will carry out a single four-minute interval at 85–95% of HRmax, rating 16–19 on Borg scale. Subjects will be instructed to strive to attain the desirable HR range within the two first minutes of the four-minute effort. All subjects will be equipped with a personal heart rate measurement device that includes Personalized Activity Intelligence (PAI), in which a high level of PAI seems to prevent or postpone CVD [31,32].

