### 2.8. Statistical Analyses

The statistical analyses will address the four research objectives stated earlier.

To elucidate the first objective, we will study the effect of shift-work on CVD-risk outcomes during a three-year follow-up using measurements at baseline and at the one- and three-year follow-ups. The primary comparison will be between the three-year follow-up and baseline. The exposure variable will be dichotomous with categories “shift-worker” and “day-worker” (reference category).

For the second research objective, we plan to use objectively measured sleep and subjectively measured sleep quality during the five-week shift period as continuous exposures variables and investigate associations to CVD risk factors. We will also include an analysis where sleep is considered a mediator between shift-work and CVD outcomes.

The third research objective concerns the effect of a three-month scheduled plant shutdown on CVD-risk outcomes. Measurements will be done before and after the shutdown, and we aim to investigate possible changes in this period.

The fourth research objective studies the effect of an eight-week HIIT intervention. We will look at the change in CVD-risk outcomes for the intervention group, and also compare this to the corresponding change for the control group. In addition to this intention to treat type analysis, we plan also to do a per-protocol analysis, where only persons having attended at least 40 percent of the training sessions will be counted as part of an HIIT group. The remaining persons will be considered to be part of the control group. We will also measure their degree of physical activity during the eight-week follow-up using the PAI index, and we will investigate whether this measure is associated with changes in the CVD-risk outcomes.

All the research questions involve longitudinal data with two or more time points. Linear and logistic mixed models will be used for all research questions. For the continuous outcomes, a linear mixed model will be used to analyze the data with a random intercept for worker, and adjustment for age, gender, and smoking. For the dichotomous outcomes, a logistic mixed model will be used with the same random-effect and fixed-effect variables. To control for multiple testing, we will use *q*-values, which is the false discovery rate equivalent for *p*-values [36].

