### Strengths and Limitation

A major strength of this study will be the comprehensive set of health measures and biomarkers used. These measures will provide in-depth information on the participating individual’s cardiovascular health, and improve knowledge on the cardiovascular health effects of shift work with night work and long working hours. The comprehensive set of biomarkers are relevant to a wide range of globally-challenging diseases, and for several of these measures, there is no or limited knowledge on their relationship to shift work.

Another strength is the controlled environment in this study, providing a detailed description of the shift organization, work hours, and sleep status of an individual level. We additionally measure factors as respirable dust exposure and physical activity, both linked to CVD risk factors [54,55], in order to gain control over other aspects which are potentially important in CVD development. This will enable us to better study effects of shift work on early manifestation of CVD.

The three-month shutdown at plant B within our study period will provide us with the opportunity to investigate whether there are any detectable changes in parameters of cardiovascular health connected to this period where participants are not exposed to shift work. In addition, the eight-week HIIT intervention carried out by the Occupational Health Service will provide great information on the effects of PA on the parameters of cardiovascular health, and additionally, will allow us to investigate the mediating effect of PA on the relationship between shift work with long working hours and CVD risk factors.

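### The shift-versus-day comparison is open to all employees but adjusted only for age, gender and smoking; education is collected and left out of the model

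*Protocol article*

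**What the plan says.** Recruitment is not limited by job. Section 2.1 states "All employees (*n* = 213) will be informed of the research project", and the expected uptake is about 60%. Section 2.2 gives medical exclusions only: "Subjects will be excluded from participation if diagnosed with severe heart or lung disease, cancer", or very high blood pressure at the examination. The Abstract describes the participants as industrial employees: "The work schedule is either rotating shiftwork (morning, evening, night) or regular day work".

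Section 2.5 gives the number of shift workers eligible for the exercise sub-study at each plant: "The intervention group will consist of all volunteering shift workers in plant A (out of 51 eligible workers") and 55 at plant B. Work tasks are described only in the subsection on the shift schedule. Section 2.6.2 mentions some former shift workers now on day work.

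Section 2.8 makes exposure dichotomous, with day workers as the reference, and takes three years versus baseline as the primary comparison. The linear mixed model has a "random intercept for worker, and adjustment for age, gender, and smoking", and the logistic model uses the same variables. Section 2.4.1 provides a "self-administered questionnaire regarding education level, work experience" and work history, among other items. The Strengths and Limitation section says that dust and physical activity are measured "in order to gain control over other aspects which are potentially important in CVD development", and that the authors will strive to account for seniority in shift work and for differences between the sexes.

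**The concern.** Workers are not allocated to shift or day work, so the groups may differ in education and kind of job as well as in working hours. Nothing confines the reference group to jobs like those of the shift workers. If social position is related to how blood pressure, lipids, inflammation markers or cIMT change over three years, and is unevenly spread between the groups, that difference in trend appears in the shift-by-time term. It would be reported as an effect of shift work. A longer study or a larger sample would not remove it.

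The article names its covariates, so this is a choice fixed in the text and not a detail left to an analysis plan. The protocol itself links kind of work to an outcome: its Discussion cites a study that found thicker cIMT in manual workers with low job control.

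**Working it through.** **1. Size of the reference pool.** Inputs: 213 employees (section 2.1), 51 and 55 eligible shift workers (section 2.5).
- Shift workers: 51 + 55 = 106.
- Others: 213 − 106 = 107, or 107/213 = 50.2%.
- At 60% participation: 0.60 × 107 ≈ 64.

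The 107 is derived. It assumes that the two eligible counts cover every shift worker; any not counted there would make the day pool smaller.

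**2. The plan's own power.** Inputs from section 2.8.2: N = 125, between-worker SD 9.3, within-worker SD 7.8, dropout 10% at one year and 20% at three years, effect 1.5–2 units per year (4.5–6 over three years). Assumed, because not stated: two-sided alpha 0.05 and a 106:107 split, which gives about 62 shift and 63 day workers.

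A random-intercept model with visits at 0, 1 and 3 years and a linear group-by-time slope has a slope SE of 0.709 units per year. Power = Φ(effect/SE − 1.96):
- 1.5/0.709 = 2.116, power 0.562.
- 2/0.709 = 2.821, power 0.806.

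The stated 0.56–0.80 is reproduced. With 70% shift workers it would be 0.492–0.734. The stated power therefore fits a reference group of about half the sample.

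**3. What can bias this contrast.** The target is change. A constant difference in level between the groups goes into the group main effect and does not touch the shift-by-time term. Only a difference in trend does. For the same reason, education as a main effect alone would do little; it has to interact with visit.

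**4. What an uncontrolled trend difference would do.** The documents give no size, so this is an illustration. With no true shift effect and SE 0.709:

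| Assumed trend difference (units/year) | Chance of a significant result |
|---|---|
| 0 | 5% |
| 0.25 | 6.4% |
| 0.5 | 10.9% |
| 1.0 | 29.2% |

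**5. Cost of restricting the reference group.** Keep 62 shift workers and remove a share f of the 63 day workers. The SE is multiplied by √[(1/62 + 1/(63(1 − f))) / (1/62 + 1/63)].

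| f (assumed) | Day workers left | SE | Power at 1.5 and 2 units/year |
|---|---|---|---|
| 0 | 63 | 0.709 | 0.56, 0.81 |
| 30% | 44 | 0.781 (+10%) | 0.48, 0.73 |
| 60% | 25 | 0.936 (+32%) | 0.36, 0.57 |

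**6. Why job category should not go into the primary model.** If office jobs have no shift-worker counterpart, a job-category-by-visit term takes up the office staff's time course entirely. They then contribute almost nothing to the shift-by-time contrast, and the primary analysis becomes the restricted one in step 5, with its loss of power.

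**The case against.** Nothing in the protocol says that day workers are office, technical or management staff. The Abstract speaks of industrial employees, and some day workers are former shift workers. A reader might infer a white-collar reference group from the open invitation, but the documents do not support that; they leave the jobs undescribed. This stands, so the point is a risk and not a demonstrated imbalance.

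The primary contrast is change, so social differences in level largely cancel. This also stands and narrows the concern to differences in trend.

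The Strengths and Limitation section shows that the authors mean to go beyond three covariates. That is true of seniority and sex, and of dust and physical activity as measured factors. None of these is education or kind of job, so the gap remains.

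Adjusting fully for job could cost more in precision than it gains in bias. Step 5 bears this out, and it rules job category by visit out of the primary model. It does not count against education, which may well overlap between the groups.

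Dust is a secondary matter. Section 2.6.2 samples six workers, and its wording does not settle whether that is six in total or six per plant; fixed particle counters are added near the production line. A reader might infer a promise of individual adjustment for dust, but the text makes none. Control can be at most at job-group or plant level.

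**Conclusion.** The point holds as a gap in the stated adjustment set for objective 1. Recruitment is open to every job, the reference group's jobs are not described, and education is collected but unused in an unrandomised comparison. About 107 employees form the day-worker pool if the 106 eligible shift workers are all there are.

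The size of any bias cannot be derived. One could assume a share of office staff and a smaller blood-pressure rise in them and so express the bias as a fraction of the planned 4.5–6 units, but neither input is in the documents and no such figure should be quoted as a finding. The false-positive rates in step 4 show sensitivity only, and rest on the assumed alpha and group split. This is an inexpensive improvement to the primary objective and does not invalidate the design.

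**What to change.** 1. In section 2.8, for objective 1, add baseline education level and its interaction with visit to age, gender and smoking. No new data are needed. The cost is a few degrees of freedom, and some precision if education is strongly related to shift status.
2. Prespecify a sensitivity analysis restricting the day-worker reference to production and maintenance jobs, identified from the questionnaire's work history where possible; section 2.4.1 does not list job category as a variable of its own. State the lower power with it: about 0.48–0.73 with 30% of day workers excluded and 0.36–0.57 with 60%, both shares being assumptions. If nearly all day workers hold such jobs, the result will barely move, which is itself informative.
3. Do not put job category by visit in the primary model.
4. In the Strengths and Limitation section, say that dust can be handled at most by job group or plant.

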#### 2.8.2. Study Power

Based on the assumption of 60% participation, we expect approximately 125 participants at baseline. Furthermore, our power calculation assumes a dropout of 10% after one year, and 20% after three years.

We consider the first research question as the primary one, and to evaluate statistical power, we focused on the effect of shift work on change in systolic blood pressure from baseline to last follow-up. We fixed the between-subject and within-subject variability to values estimated in a similar longitudinal study [37], i.e., we assumed a between-worker standard deviation of 9.3 and a within-worker standard deviation of 7.8. Furthermore, we assumed an effect size corresponding to a yearly increase of 1.5–2 units in blood pressure in the shift group compared with the reference group of day workers. Based on these assumptions, we obtained a power of 0.56–0.80 of getting a significant effect of shift work on change in systolic blood pressure. However, to better account for the fact that we have multiple outcomes, we took this power analysis one step further. We assumed that of the variables included in our study, 1/3 had an effect size of the same magnitude as for the systolic blood pressure, while for the other 2/3 of the outcomes, we assumed there were no effects of shift-work exposure. We adjusted the *p*-values for multiple-testing using a Bonferroni correction and obtained a power of 0.57–0.95 of getting at least one significant finding when adjusted for multiple testing.

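### Q-values over only about 20 to 24 outcomes: if the null share is estimated, the realised false discovery rate can be two to three times an intended 5%; fixing that share at 1 avoids this

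*Protocol article*

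**What the plan says.** Section 2.8 applies one multiplicity rule after describing the models for all four objectives: "To control for multiple testing, we will use *q*-values, which is the false discovery rate equivalent for *p*-values". It does not say how the null share is obtained, what q counts as a finding, or which tests form a family.

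Section 2.8.2 makes the first research question primary. For one outcome it reports that "we obtained a power of 0.56–0.80 of getting a significant effect of shift work on change in systolic blood pressure". It then supposes that of the study variables "1/3 had an effect size of the same magnitude as for the systolic blood pressure", with no effect on the rest, and states: "We adjusted the *p*-values for multiple-testing using a Bonferroni correction and obtained a power of 0.57–0.95 of getting at least one significant finding".

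The number of outcomes is not given. It has to be counted from the measurement sections.

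**The concern.** The q-value differs from a Benjamini-Hochberg adjusted p-value by one factor, the estimated null share. That factor buys power when there are very many tests, because π0 can then be read from the flat right-hand part of the p-value histogram. With two dozen p-values that part holds a handful of points, and the estimate can fall far below the truth, even to zero. Every p-value is then shrunk by too much.

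The study measures many markers and will report those that pass. If the realised false discovery rate is 10 to 15% where the reader assumes 5%, associations between shift work and cardiovascular markers will be reported with less protection than the method's name suggests.

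**Working it through.** **1. Number of tests for objective 1** (sections 2.4.2 to 2.4.7)

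- Cholesterol, LDL, HDL, HbA1c, CRP: 5
- Six-plex cytokine panel plus adiponectin: 7
- Systolic and diastolic pressure, resting heart rate: 3
- Central pressure, augmented pressure, augmentation index, pulse wave velocity: 4 (5 with central pulse pressure)
- Mean cIMT, maximal cIMT, plaque score: 3
- VO2max: 1

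Total: 5 + 7 + 3 + 4 + 3 + 1 = 23, or 24 with central pulse pressure. Merging near-duplicates gives about 20. Other objectives have fewer: the eight-week visit drops cIMT (2.6.1), and the shutdown visits drop cIMT and VO2max (2.6.3).

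**2. The plan's own power figure**

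Inputs from 2.8.2: "we assumed a between-worker standard deviation of 9.3 and a within-worker standard deviation of 7.8"; "a yearly increase of 1.5–2 units in blood pressure in the shift group compared with the reference group of day workers"; "we expect approximately 125 participants at baseline"; dropout 10% at one year and 20% at three. Assumed: two-sided 5%, and half the sample on shifts (section 2.5 gives 51 + 55 = 106 eligible shift workers, of 213 employees).

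- Two-point check: N = 125 × 0.8 = 100, 50 per group. SE = 7.8 × √2 × √(2/50) = 2.21. The effect over three years is 4.5 to 6. Power = Φ(4.5/2.21 − 1.96) = 0.53 to Φ(6/2.21 − 1.96) = 0.78.
- Random-intercept model at 0, 1 and 3 years: SE of the slope difference is 0.709. Power = Φ(1.5/0.709 − 1.96) = 0.56 to Φ(2/0.709 − 1.96) = 0.81.

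The stated 0.56 to 0.80 is reproduced. It corresponds to mean z-statistics of about 2.11 and 2.80, which were used as the true effects below.

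**3. Why π0 is unstable here**

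With p-values ordered from smallest to largest:

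q(i) = min over j ≥ i of π0 × m × p(j) / j, where π0(λ) = #{p > λ} / [m(1 − λ)].

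The spline method smooths π0(λ) over λ = 0.05 to 0.95 and reads it at 0.95. With 24 independent true nulls, the expected count above 0.95 is 24 × 0.05 = 1.2. The chance of no p-value there is 0.95^24 = 0.29 (0.95^20 = 0.36 with 20 tests). Even at λ = 0.5, the standard deviation of π0(λ) is √(24 × 0.25)/12 = 0.20.

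**4. Simulation**

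20,000 data sets per setting; m = 20 to 24 two-sided normal tests; findings at q ≤ 0.05 (assumed); correlation zero or modest (0.3, or moderate within blocks). Either no outcome has an effect, or about 1/3 do, as in 2.8.2.

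| Choice of π0 | Realised false discovery rate |
|---|---|
| π0 = 1 (Benjamini-Hochberg) | 0.03–0.05 |
| Fixed λ = 0.5 | about 0.055–0.065 (single settings 0.05–0.07) |
| Bootstrap, π0 ≤ 0 discarded | about 0.07 |
| Bootstrap, π0 ≤ 0 kept | 0.11–0.18 |
| Spline, π0 ≤ 0 discarded | 0.10–0.12 |
| Spline, all data sets | 0.10–0.15 |

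The spline estimate is zero or below in about 1 to 7% of these data sets, and the bootstrap estimate in about 5 to 19%.

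**5. What drives it**

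- Correlation: with 24 tests, no true effect and failed estimates discarded, the spline gives about 0.10 both at zero correlation and at 0.3. Correlation matters more at 0.7, where fixed λ gives 0.08–0.12 and the spline 0.08–0.23 depending on how failures are handled.
- Number of tests: for the spline at correlation 0 to 0.3, the rate falls to 0.07–0.09 with 48 tests and 0.06–0.08 with 96.
- Cut-off: at q ≤ 0.10 the spline gives 0.17–0.22.

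**6. Bonferroni figure**

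With 20 tests, 6 of them with effects, and zero correlation, the Bonferroni chance of at least one finding is 0.71 to 0.96. At correlation 0.3 it is 0.58 to 0.87. The stated 0.57 to 0.95 is plausible if its range spans correlation as well as effect size.

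**The case against.** The strongest reply is that the article fixes none of the things that determine the size. The source cited for q-values is not at hand. Benjamini-Hochberg adjusted p-values are often reported under the same name, so the sentence does not exclude the remedy proposed here. Estimator, cut-off and family are details an article may leave to an analysis plan. All of this stands, and the size must be given as conditional. It does not remove the point: a q-value as ordinarily defined uses an estimated null share, and that suits this number of tests badly.

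Three stronger readings are tempting, and the documents support none of them.

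- A reader might infer that the plan doubles or triples the error rate it promises. It promises no rate; 5% is an assumption here. The factor of two to three belongs to the spline, or to a bootstrap whose failed estimates are accepted as they stand.
- A reader might blame correlated markers that turn significant together. Correlation is not the main driver. Wholesale significance arises when an estimate of zero is taken at face value, and nothing says the analysts would do that. Discarding such estimates still leaves about 0.10–0.12 with the spline, and the analyst would then have to choose another method after seeing the data.
- A reader might see an error in the power section, where "We adjusted the *p*-values for multiple-testing using a Bonferroni correction" while the analysis uses q-values. At the same level, Benjamini-Hochberg rejects something whenever Bonferroni does, and a q-value with π0 ≤ 1 rejects at least as much. The Bonferroni power is therefore a conservative bound for at least one finding.

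**Conclusion.** The point holds in conditional form. The plan names a multiplicity method whose distinctive ingredient, the estimated null share, cannot be estimated reliably from about 20 to 24 p-values. Depending on the estimator and the handling of failures, an intended 5% becomes anything from about 5.5% to 18% at zero or modest correlation; with π0 = 1 it stays at 3 to 5%.

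This rests on an assumed cut-off of 0.05, normal test statistics, one family per objective and the outcome count above. Pooling objectives would shrink the inflation, and it is absent if π0 = 1 is already intended. This is a cheap improvement and does not invalidate the design.

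**What to change.** In section 2.8, replace the q-value sentence with a statement that Benjamini-Hochberg adjusted p-values (equivalently, q-values with π0 fixed at 1) will be used within the outcomes of each objective.

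This takes one sentence and one software option. The price is somewhat fewer discoveries: in the plan's scenario with effects on 1/3 of outcomes, the chance of at least one finding is about 0.71–0.99, against 0.82–0.99 with the spline. A uniform correlation of 0.3 lowers both, to about 0.61–0.92 and 0.74–0.96. Part of what is given up is the extra false findings. The power section needs no change, because its Bonferroni figure remains a lower bound.
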